## Abstract

**Background:**

One in 4 young adults has prediabetes, and improving diet is a key step to lowering the risk of diabetes. Existing standard-of-care diet approaches show short-term efficacy but lack long-term effectiveness, including in young adults. Greater fiber intake is associated with a reduced risk of diabetes; however, fiber is not well targeted using existing interventions. Many young adults may be reluctant to consume fiber given the coexistence with digestible carbohydrates and concerns over gastrointestinal effects. Targeting these factors more explicitly may improve uptake and lower diabetes risk, and doing so via a mobile health (mHealth) intervention may be particularly responsive to young adult demands.

**Objective:**

This study aims to establish and preliminarily test the feasibility of a highly innovative and scalable mHealth-based intervention to improve fiber intake among young adults with prediabetes.

**Methods:**

This single-arm feasibility study includes 2 phases to preliminarily test an mHealth-based fiber intervention (phase 1) and elucidate factors that impact sustained behavior change and fiber intake after intervention end using ecological momentary assessment (EMA; phase 2). The intervention is 3 months in length and features daily EMAs with responsive text–based coping messages to target key predictors of fiber intake. EMAs will also be paired with brief (ie, <1 minute) educational videos on fiber delivered once per day. Participants will also receive weekly home-delivered high-fiber food packages and wear a continuous glucose monitor at 2 time points during the intervention as a form of biofeedback. At the baseline and postintervention time points, fasting blood glucose, hemoglobin A_1c_, and insulin resistance (Homeostatic Model Assessment of Insulin Resistance) will be assessed. After the postintervention time point, participants will continue with daily EMAs to assess factors associated with sustained fiber intake. Diet will be assessed using Automated Self-Administered 24-hour dietary recalls at the baseline and postintervention time point and after the phase 2 EMA.

**Results:**

This study was initiated in July 2025. As of March 2026, the mHealth intervention content is being built, with app completion and trial enrollment both slated to begin in April 2026.

**Conclusions:**

The results of this study will provide pivotal evidence on the utility of a fiber-focused intervention delivered via mHealth with biofeedback and home-delivered foods to lower the risk of diabetes in young adults with prediabetes.

## Introduction

One in 4 young adults has prediabetes [1]. Diet is instrumental in diabetes prevention [2]. Existing standard-of-care diet approaches (eg, Diabetes Prevention Program; DPP) promote a negative energy balance via multiple behaviors (eg, decreased fat intake, decreased processed food intake, counting calories, etc). This negative energy balance enables weight loss, which staves off diabetes development. While the DPP shows short-term efficacy for decreasing the incidence of diabetes, in the long term, DPP participants are nearly identical to controls as weight gain is still observed long after intervention completion [3]. These null effects are particularly pronounced in young adults [3].

Key limitations of the DPP and similar complex interventions are the incompatibility of intervention mechanisms with daily life [4]. That is, maintaining a negative energy balance without ongoing, intensive intervention is exceedingly difficult. End users report a desire for alternative interventions that promote behaviors that are easier to maintain without intervention, including via the use of clear messaging [4-6]. When interventions are more easily maintained, adherence improves, ultimately improving behavior adoption and long-term disease risk reduction [4].

Interventions focused singularly on improving fiber intake offer a simplified approach to modifying behavior [5,7,8]. Fiber interventions perform similarly and, in some ways, are superior to complex alternatives [5,7,9]. In addition, regular intake of fiber—a nondigestible carbohydrate found only in plant foods—is associated with significantly lower diabetes risk [10-12]. Higher intake of fiber from grains (eg, wheat) is associated with 10% to 11% lower diabetes risk [2,12], higher intake of legumes is associated with 35% lower diabetes risk [13], higher intake of nuts is associated with 35% to 43% lower diabetes risk [12], and higher intake of vegetables is associated with 4% lower diabetes risk [2]. Fiber improves glycemic control via multiple mechanisms, including delayed gastric emptying, increased satiety, decreased glucose absorption, decreased inflammation, and increased uptake of glucose into muscle tissue [14-16]. Interventions focused on fiber can also address the fact that fiber intake has been insufficient for decades, with adults eating approximately 16 grams per day, nearly half the recommendation [17-19]. Fiber is mentioned in interventions such as the DPP but only briefly. Thus, post-DPP fiber intake does not improve to levels that are meaningful (17.8 g fiber per 2000 kcal vs the recommended amount of >28 g per 2000 kcal [17,18,20]). Some of the known effects of fiber (eg, delayed gastric emptying and microbiota modulation) can also lead to gastrointestinal (GI) side effects that may be perceived as uncomfortable, discouraging intake over time [21,22]. These are not explicitly targeted as part of many standard intervention approaches. More directly targeting these, including the use of anticipatory guidance and coping messages, may improve uptake of fiber recommendations.

Interventions that place a singular emphasis on fiber may improve outcomes given the simplified intervention approach and distinct health effects of fiber. Research has shown that fiber intake is a top predictor of long-term success following interventions [23]. Ma et al [5] found that an in-person intervention with a “single-component” goal of increasing fiber intake significantly improved insulin resistance compared to a “multicomponent” goal of adhering to all American Heart Association diet recommendations. The intervention included a combination of group classes and counseling over 12 months. Intervention engagement was only 56%, so there was room for improvement in intervention delivery; however, the content appears promising [5]. Mobile health (mHealth) interventions hold the potential to increase engagement due to the ubiquity of mobile phones [4]. mHealth-based DPP versions show high retention (>80%) [24,25], whereas young adult–specific mHealth interventions improve other markers of diet quality (eg, vegetable intake) [26]. Few, if any, mHealth interventions have been used to target fiber intake. mHealth interventions may also address common reluctance to procure unfamiliar foods by augmenting with home delivery of high-fiber foods [27]. Tester and Leak [9] found that sending high-fiber foods to adults significantly improved fasting glucose and measures of insulin resistance.

There is also a desire for mHealth interventions that include biofeedback, or “direct feedback about the body using external monitoring devices” [4,28]. Continuous glucose monitors (CGMs) are used in diabetes treatment but less as a diet-focused behavior change tool in prediabetes. CGMs have been used as a behavior change tool to promote exercise in adults with diabetes or prediabetes, improving goal setting, exercise, and waist circumference (*P*<.05) [29]. Use of CGMs may also address emerging concerns regarding fiber’s glycemic effects. As fiber is a carbohydrate and is often present with other digestible carbohydrates such as starch, there may be fear that fiber—or foods that contain fiber—should be avoided [30]. In pursuit of simplified interventions, other approaches (eg, carnivore diets) that eliminate carbohydrates and plants in total have grown popular. This has led to a potential collateral demonization of fiber [31,32]. This is unfortunate given that fiber from whole foods—even whole foods high in carbohydrates, such as cereal grains and legumes—are associated with lower diabetes risk [12,33].

Short-term changes in behavior are common in diet interventions; however, achieving changes that are sustained after the intervention remains elusive [3]. Ecological momentary assessments (EMAs) are often used to assess dynamic factors that contribute to behavior [34] and can be used to elucidate sustained intervention response [35]. Monitoring behavior after an intervention is common in tobacco- and alcohol-focused EMA studies [35]. However, diet-focused EMA studies more commonly assess diet itself (eg, foods eaten) or nonfood factors (eg, stress) during the intervention [36-40]. For example, Goldstein et al [40] used EMA during a 12-month weight loss intervention to assess behavior that influenced response during the intervention (eg, feeling deprived predicted eating unintended foods; *P*<.05) but not after the intervention. Moreover, little work exists using EMA to measure response to fiber ingestion, which could fill key knowledge gaps regarding how fiber affects appetite and behavior. In a 3-year weight maintenance intervention, Zhu et al [41] found that fiber intake was associated with improved satiety but increased desire to eat; however, this study assessed these factors at 5 separate weeks throughout the 3-year period, offering little insight into dynamic effects. Therefore, the objective of this study is to establish and preliminarily test the feasibility of a highly innovative and scalable mHealth-based intervention to improve dietary fiber intake among young adults with prediabetes.

## Methods

### Study Design

On the basis of our primary study outcome (feasibility), we will conduct a 2-phase single-arm study [42,43] to preliminarily test our mHealth-based fiber intervention in up to 80 young adults with prediabetes (phase 1) and elucidate factors that impact sustained behavior change and fiber intake after intervention end using EMAs (phase 2) (Figure 1).

**Figure 1. F1:**
[figure not shown]
Study design and schematic. CGM: continuous glucose monitoring; EMA: ecological momentary assessment; mHealth: mobile health.

### Theoretical Framework

The theoretical framework for this intervention is a combination of self-determination theory (SDT), social cognitive theory (SCT), and the biopsychosocial model [44-46]. In brief, the intervention taps into SDT given that it honors individual autonomy (eg, allows for flexibility in the remainder of the diet outside of fiber), promotes competence (eg, targets knowledge), and promotes relatedness (eg, use of interactive mHealth content). It also taps into SCT given that it alters cognitive processes and integrates suggestions from previous participants (observational learning). Finally, it intentionally integrates elements of coping to address the expected yet physiologically normal GI responses that can occur with increased fiber ingestion [21,22]. These messages are informed by both cognitive behavioral therapy and acceptance and commitment therapy, featuring elements of anticipatory coping (eg, preparing individuals for potential symptoms), behavioral coping strategies (eg, gradual fiber increases, hydration, and symptom monitoring), and elements of cognitive reframing [47].

### Participants

We will recruit young adults aged 18 to 39 years who have prediabetes [48]. Classification of prediabetes is based on having a hemoglobin A_1c_ (HbA_1c_) level between 5.7% and 6.4% per American Diabetes Association guidelines [49]. Other inclusion criteria are residing in or near Tulsa, Oklahoma (where in-person data collection will take place), or nearby and being willing to travel for visits; ability to access and/or use a smartphone; and proficiency in the English language. Exclusion criteria are a suspected eating disorder based on the 26-item Eating Attitudes Test (which was reproduced with permission [50]), current use of a glucagon-like peptide-1 receptor agonist, food allergies or intolerances that preclude engagement, self-reported diagnosis of irritable bowel syndrome or inflammatory bowel disease, self-reported pregnancy or breastfeeding, or travel plans that limit intervention completion.

### Recruitment

Participants will be recruited via community events; email distributions to students, faculty, and staff at the University of Oklahoma; directly via the medical record system of the University of Oklahoma Health Campus (MyChart); social media advertisements; provision of flyers at university health screenings; and direct communication and distribution of flyers in the clinics within internal medicine at the University of Oklahoma Health Campus in Tulsa. Prospective participants can provide documentation of an HbA_1c_ level within the prediabetes range from the previous 3 months or complete the Centers for Disease Control and Prevention Prediabetes Risk Test as part of the study screening. If prospective participants are otherwise eligible and appear to be at risk of prediabetes per the Prediabetes Risk Test, they will be invited to attend an in-person recruitment visit wherein they can complete the informed consent process, followed by a screening HbA_1c_ test. If their HbA_1c_ level is within the prediabetes range, they will be eligible for enrollment in the study. If their HbA_1c_ level is not within the prediabetes range, their participation will be considered complete, and they will be deemed ineligible.

### Ethical Considerations

University of Oklahoma Health Campus Institutional Review Board approval was obtained on August 18, 2025. Written informed consent will be obtained from all individuals in person prior to any study-related screening of HbA_1c_ and (if eligible) study participation. During the informed consent process, participants will be informed of potential risks, including those that are expected to occur with increases in fiber intake (eg, GI discomfort). Participants will receive compensation in the form of gift cards for completion of initial HbA_1c_ screening (US $15), US $50 for the follow-up visit if applicable, and up to US $168 for EMAs across both phases (up to US $84 for phase 1 and up to US $84 for phase 2). Rates of EMA compensation will be based on the rate of EMA completion: participants who complete 50% (42/84) to 73.8% (62/84) of EMAs will receive a US $42 gift card, those who complete 75% (63/84) to 89.3% (75/84) of EMAs will receive a US $63 gift card, and those who complete 90.2% (>75/84) or more will receive a US $84 gift card [51].

Data will be primarily collected in REDCap (Research Electronic Data Capture; Vanderbilt University). EMA data will be collected in the University of Oklahoma Health Campus OU Health Stephenson Cancer Center mHealth Shared Resource (Insight). No protected health information will be stored or transmitted via Insight. CGM data will be accessed via participant Clarity app or Dexcom accounts for data extraction. All data will be ultimately coded and saved on OU Health specific platforms and/or REDCap. EMA and CGM data will be monitored for the corresponding intervention periods. If blood glucose levels remain abnormally elevated, consultation with the remainder of the team (eg, [name] and [name]) will be made, and appropriate action will be taken. Participants will also be given guidance on actions to take if blood glucose remains high. In addition to study team contact information, participants will be provided with an individualized REDCap link to report any adverse events, which will be promptly reviewed by the research team and reported according to (1) whether they were related to the study, (2) whether they were anticipated, and (3) level of severity. Participants will be told that, if any foods or procedures cause discomfort, they are free to refrain from eating those foods or completing those procedures without compromising total participation in the study.

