To assess feasibility of the intervention, we will evaluate the following metrics according to Bowen et al [57]: implementation, demand, acceptability, and preliminary efficacy. Implementation will be assessed via review of message delivery, which will be automatically tracked on Insight. We will also track delivery of high-fiber food packages and CGM provision as defined in the protocol. For demand, we will assess participant retention in the trial as reflected by completion of data collection activities, as well as intervention uptake. Intervention uptake will be assessed via the percentage of all delivered content viewed by participants on Insight, use of CGMs by participants for the total duration requested, and participant report of consumption of provided high-fiber foods. For acceptability, we will provide acceptability surveys at the postintervention time point that include Likert-scale questions. Finally, for preliminary efficacy, we will leverage data collection on HbA_1c_ and the HOMA-IR.

#### Phase 2

After completion of the intervention and phase 1 postintervention data collection, participants will begin an observation-only period of EMA that spans 4 weeks. During this time, they will receive no intervention but complete EMAs 3 times a day as in the run-in period. EMA variables will be the same as during phase 1. Then, after completion of this period, they will repeat 2 more random, unannounced ASA-24 measures for fiber intake (“post-observation” time point).

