#### Analytic Plan

For phase 1, we will compute descriptive statistics (for all feasibility metrics) and 2-tailed paired *t* tests to examine changes in our preliminary efficacy outcomes (fiber intake, HbA_1c_, and HOMA-IR) from baseline to the postintervention time point as a measure of preliminary efficacy. For phase 2, the primary goal is to determine whether participants maintain fiber intake after the intervention and identify real-time factors that predict adherence. Adherence will be defined as maintaining fiber intake at or above 80% [59] of postintervention levels based on ASA-24 data at the start and end of the 4-week EMA period. A logistic multilevel model will be used to predict adherence (1=maintained; 0=dropped below threshold) from EMA-measured factors (eg, affect). EMA predictors will be aggregated at the participant level (eg, mean stress across the EMA period) to assess overall exposure to these factors, whereas daily fluctuations will be modeled using within-person deviations from each participant’s mean. To assess how the influence of these predictors changes over time, we will use time-varying effect modeling, allowing for the examination of whether certain factors (eg, stress) exert stronger effects on adherence early vs late in the observation period. Additionally, we will explore the role of EMA variability, calculating within-person fluctuations (eg, SD of stress) to test whether greater instability in these factors predicts lower adherence. We will assess patterns of missing data and conduct sensitivity analyses assuming different missing data mechanisms. For example, we will consider a multiple imputation approach, which uses baseline characteristics to account for potential missing at random mechanisms [60,61].

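### The two final diet recalls that decide phase 2 adherence have no listed payment, and the planned n=64 allows for no loss of them

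*Protocol article*

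**What the plan says.** **Payments (Ethical Considerations).** Two fixed gift cards are set out as "completion of initial HbA_1c_ screening (US $15), US $50 for the follow-up visit if applicable". A further, variable amount rewards answering the app's prompts and is given as "up to US $168 for EMAs across both phases (up to US $84 for phase 1 and up to US $84 for phase 2". For this last item the article adds that "Rates of EMA compensation will be based on the rate of EMA completion", in three tiers out of 84 prompts. No line mentions an ASA-24 recall.

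**Final measurement (Data Collection, Phase 2).** Participants complete EMAs three times a day for four weeks without intervention. Then, "after completion of this period, they will repeat 2 more random, unannounced ASA-24 measures for fiber intake". No visit or other paid activity is described at or after that point.

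**Outcome (Analytic Plan).** Adherence means fiber intake of at least 80% "of postintervention levels based on ASA-24 data at the start and end of the 4-week EMA period". A logistic multilevel model is to "predict adherence (1=maintained; 0=dropped below threshold) from EMA-measured factors (eg, affect").

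**Sample size (Power).** The phase 2 sample is 64, from 80% retention at the postintervention visit, with 75% EMA compliance. No completion rate is applied to the post-observation recalls.

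**Missing data (Analytic Plan).** Patterns of missingness will be assessed and sensitivity analyses run under different mechanisms. The one example is multiple imputation from baseline characteristics under missing at random.

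**The concern.** Incentive and information are mismatched. A missed EMA prompt costs one of 84 predictor records. A participant who gives neither final recall has no observed outcome, so none of that participant's EMA records has an observed adherence value to predict. Yet the listed phase 2 payment rewards only the prompts.

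The recalls also come when the study has least hold on participants: food deliveries and videos stopped four weeks earlier, the visits are over, and the recalls are unannounced. If people who have returned to a low-fiber diet are less willing to report what they eat, maintenance among completers would look better than it is. The factors associated with lapse would then be estimated from a sample short of lapsers.

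**Working it through.** **1. Payments listed.** US $15 + US $50 + US $168 = US $233 at most. The US $84 for phase 2 covers 3 × 28 = 84 prompts. The amount tied to any recall is US $0.

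**2. The plan's own figures.**
- Participants: 80 × 0.80 = 64.
- Morning diaries: 64 × 28 × 0.75 = 1344.
- Effective sample size with first-order autoregressive correlation 0.7: 1344 × (1 − 0.7)/(1 + 0.7) = 237.2, which matches the stated 237.
- Power at f² = 0.034, one predictor, two-sided alpha 0.05 (alpha is assumed): 80.7%, which matches the stated 80%.

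These figures reproduce, and they include no loss at the final recalls.

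**3. Loss unrelated to lapse.** Each 10% missing removes 0.10 × 64 = 6.4 outcomes. The rates below are assumptions.

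| Final recalls missing | Participants with outcome | Effective N | Power at f² = 0.034 |
|---|---|---|---|
| 0% | 64 | 237 | 80.7% |
| 10% | 58 | 215 | 76.8% |
| 20% | 51 | 189 | 71.3% |
| 30% | 45 | 167 | 65.8% |

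The power column is only indicative. The plan's calculation concerns sleep and fiber intake at diary level, not the participant-level binary outcome. If its fiber measure is the diary checklist, missing recalls would not affect it.

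For the maintenance rate itself, at 60% the standard error is √(0.6 × 0.4/64) = 6.1 points with 64 outcomes and √(0.6 × 0.4/51) = 6.9 points with 51. Equal loss introduces no bias in this rate: 0.6 × 0.9/(0.6 × 0.9 + 0.4 × 0.9) = 60%.

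**4. Loss related to lapse.** Let p be true maintenance, and c₁ and c₀ the recall completion of maintainers and lapsers. Observed maintenance = p·c₁ / [p·c₁ + (1 − p)·c₀]. With p = 0.60 (all inputs assumed):

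| c₁ | c₀ | Calculation | Observed |
|---|---|---|---|
| 90% | 80% | 0.54/0.86 | 62.8% |
| 90% | 70% | 0.54/0.82 | 65.9% |
| 90% | 60% | 0.54/0.78 | 69.2% |
| 85% | 55% | 0.51/0.73 | 69.9% |

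The upward bias of about 3 to 10 points compares with a standard error of about 6.

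**5. What a missing-as-not-maintained analysis would show.** In the 90%/70% case it gives 0.60 × 0.90 = 54%, against 65.9% among completers. In the 85%/55% case it gives 0.60 × 0.85 = 51%, against 69.9%. In both cases the pair brackets the true 60%.

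**The case against.** A reader might infer that outcome data will be lost, and mainly from participants who lapsed. The article does not support that. It gives no recall completion rate, and nothing in it links lapse to non-response. The percentages in step 4 follow from their assumed inputs.

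A reader might also infer that the recalls are certainly unpaid. The article lists no payment, but it may condense a fuller schedule, and it does not say when the phase 2 card is issued. If the card is held until the recalls are done, some incentive exists, although its amount still depends only on EMA completion. The US $50 visit payment may likewise cover the postintervention recalls, which serve as the reference level and have no line of their own.

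Nor is it right that a participant without final recalls contributes nothing. The morning diary includes a high-fiber food checklist, and phase 2 uses the same EMA variables, so up to 28 daily reports remain. The planned sensitivity analyses are a real safeguard and are not confined to missing at random.

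Finally, the primary outcome is feasibility, and retention is already defined through completion of data collection activities, so recall completion should be reported in any case.

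These points limit the concern to a risk but do not remove it. The only named method conditions on baseline characteristics, which cannot capture a lapse that happens after the intervention. No analysis restores outcomes that were never observed in a sample of about 64.

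**Conclusion.** The concern holds as a design weakness that is cheap to correct. The listed incentives reward screening, the follow-up visit and EMA completion, while the phase 2 adherence outcome rests on recalls that appear in no payment line and for which n=64 makes no allowance.

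Its size depends on quantities that the article does not give. Loss unrelated to lapse costs about 6 of 64 outcomes per 10% missing and does not bias the maintenance rate. Loss concentrated among lapsers would move a true 60% to between 63% and 70% under the completion rates assumed above. The feasibility objective of phase 1 is not affected.

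**What to change.** Before enrollment begins:

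1. **Payment.** Tie a modest part of the existing phase 2 amount to completion of the post-observation recalls, regardless of reported intake and of EMA rate. Leave the exact split to the investigators, adjust the EMA tiers to match, and state when the card is issued.
2. **Imputation.** Include the phase 2 EMA data, especially the high-fiber food checklist, in the imputation model alongside baseline characteristics. This makes missing at random more credible, though less so for participants who also stop answering EMAs.
3. **Sensitivity analysis.** Add one that counts missing final recalls as not maintained, reported beside the completer result.
4. **Sample size.** State the assumed recall completion next to n=64.

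The cost is a change of consent and IRB wording and a slightly lower incentive per EMA prompt, which bears on the 75% compliance assumption. The total budget is unchanged. Items 2 to 4 need only text and analysis time.
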